***Tertiary endpoints***

*Time to presence of asexual stage P. falciparum parasites during the ten-month efficacy follow-up period* – Similar analyses as those described for the primary endpoint will be performed.

*Time to parasite density  50,000 asexual stage P falciparum parasites per microliter of blood during the ten-month efficacy follow-up period* – Similar analyses as those described for the primary endpoint will be performed.

*Presence of MSP-1 3D7 parasites in clinical cases of malaria meeting the primary case definition during the ten-month efficacy follow-up period* – Frequencies and percentages of cases with circulating MSP-1 3D7 parasites will be calculated by vaccine study group.

*Presence of MSP-1 3D7 parasites at a given cross-section survey time during the ten-month efficacy follow-up period* – For a given survey time, the frequency and percentage of subjects with circulating MSP-1 3D7 will be calculated by vaccine study arm.

*Time to anemia defined as hemoglobin level < 8.0 g/dl during the ten-month efficacy follow-up period* – Similar analyses as those performed for the primary endpoint will be conducted. In addition, a Cox model with vaccine study arm, baseline hemoglobin, and age as covariates will be applied to the data. The six-month cumulative incidence rate of anemia will be calculated for each vaccine study arm.

### Analysis of Immunogenicity

Antibody responses as measured by anti-MSP142 (3D7) IgG ELISA at Study Days 0, 29, 57, 85, 171, 256, and 340 will be evaluated. For each vaccine group and time point, the geometric mean titer and its standard deviation will be calculated and presented in tables and graphs. In addition, longitudinal mixed effects models will be utilized with log10-transformed antibody titers as the response variable and vaccine group and time since first vaccination as predictor variables. The effect of baseline variables such as age and gender on antibody kinetics will be explored with such models as well.

Additional analyses will calculate the area-under-the-curve (AUC) for antibody titers for each subject and compare average AUC between vaccine study arms.

A Cox proportional hazards model with log10-transformed antibody titer as a time-dependent covariate will be applied to the data on time to clinical malaria using the primary case definition to assess the association between antibody titers and subsequent risk of clinical malaria.

Similar analyses as described above will be applied to data on MSP142 fragment- specific antibody titers.

For subjects vaccinated with FMP1/AS02A, the relationship between antibody levels measured by IgG ELISA and by competition ELISA will be explored through scatter plots and calculation of the correlation coefficients at each time point. Likewise, the relationship between antibody levels measured by growth inhibition assay and by ELISA will be assessed.

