***Safety and Immunogenicity***

- To assess solicited adverse events occurring in the seven days following each dose of vaccine
- To assess unsolicited adverse events occurring in the 30 days following each dose of vaccine
- To assess serious adverse events occurring after the first dose of vaccine to the end of the EFP
- To assess the immunogenicity of the FMP1/AS02A malaria vaccine from the first dose of vaccine to the end of the EFP
- To assess the association between MSP-1 antibody titers and the subsequent risk of clinical malaria during the EFP

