### Immunogenicity Cohort

For purposes of study data analysis, the “immunogenicity cohort” will include all subjects for whom assay results are available for antibodies against the specified study vaccine antigen component or the comparator. There are no standard cut‑off titers for seropositivity determinations in general use for the MSP-1 assay.

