#### Clinical vaccine efficacy

***Primary endpoint***

*Time to first episode of clinical malaria during the six-month efficacy follow-up period using the primary case definition* – The logrank statistic and corresponding p‑value will be calculated to test the null hypothesis of no difference in the distribution of time to clinical malaria between the FMP1/AS02A and rabies vaccine groups. A Cox proportional hazards model with an indicator variable for vaccine group will be fit to the data and an estimate of the hazard ratio along with its corresponding 95% confidence interval will be computed. Vaccine efficacy will be defined as one minus the hazard ratio. Additional Cox models may explore the effects of age, sex, bed net use as reported at baseline, nearest field station, and hemoglobin genotype on vaccine efficacy. Kaplan-Meier curves for time to clinical malaria will be generated by vaccine group. An alternative estimate of vaccine efficacy based on cumulative incidence rates will be calculated as well.

The primary data analysis will be conducted with the ATP cohort; however, a similar analysis based on the ITT cohort will be performed to assess the robustness of the analysis based on the ATP cohort.

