#### Biological effects

***Secondary endpoints***

*Time to presence of asexual stage P. falciparum parasites during the six-month efficacy follow-up period* – Similar analyses as those described for the primary endpoint will be performed.

*Time to parasite density  50,000 asexual stage P falciparum parasites per microliter of blood during the six-month efficacy follow-up period* – Similar analyses as those described for the primary endpoint will be performed.

*Presence of MSP-1 3D7 parasites in clinical cases of malaria meeting the primary case definition during the six-month efficacy follow-up period* – Frequencies and percentages of cases with circulating MSP-1 3D7 parasites will be calculated by vaccine study group.

*Presence of MSP-1 3D7 parasites at a given cross-section survey time during the six-month efficacy follow-up period* – For a given survey time, the frequency and percentage of subjects with circulating MSP-1 3D7 will be calculated by vaccine study arm.

*Time to anemia defined as hemoglobin level < 8.0 g/dl during the six-month efficacy follow-up period* - Similar analyses as those performed for the primary endpoint will be conducted. In addition, a Cox model with vaccine study arm, baseline hemoglobin, and age as covariates will be applied to the data. The six-month cumulative incidence rate of anemia will be calculated for each vaccine study arm.

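### The antibody-risk Cox model names titer as its only covariate in a cohort covering both arms; run as written, its coefficient would mix arm, within-arm risk and exposure

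*Protocol*

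**What the plan says.** Protocol Section 5.2 lists as a secondary objective: "To assess the association between MSP-1 antibody titers and the subsequent risk of clinical malaria during the EFP". Section 12.4.3 supplies the analysis, a Cox model in which log10 titer varies over time. It "will be applied to the data on time to clinical malaria using the primary case definition to assess the association between antibody titers". The same section extends these analyses to titers against MSP-1 fragments. No other term, stratum or restriction is named for this model. The immunogenicity cohort (Section 12.2.4) "will include all subjects for whom assay results are available for antibodies", so it is not limited to one arm.

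Elsewhere the protocol writes such details out:

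- The primary Cox model (Section 12.4.2) has a vaccine-group indicator.
- For anemia, Section 12.4.2 adds "a Cox model with vaccine study arm, baseline hemoglobin, and age as covariates will be applied to the data".
- The mixed models for titer (Section 12.4.3) list vaccine group and time as predictors.
- Restriction to vaccinees appears two paragraphs after the antibody-risk model, for a different purpose: "For subjects vaccinated with FMP1/AS02A, the relationship between antibody levels measured by IgG ELISA and by competition ELISA will be explored".
- Exposure-type covariates are named only for the efficacy models: "Additional Cox models may explore the effects of age, sex, bed net use as reported at baseline, nearest field station, and hemoglobin genotype".

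Section 12.4 leaves further detail to a Reporting and Analysis Plan (RAP). Section 12.1.2 says the secondary endpoints are for insight and not for formal claims.

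**The concern.** Vaccination is meant to raise MSP-1 titer, so across both arms titer is partly a marker of the randomized arm. A vaccine effect by any mechanism would then appear as an inverse relation between titer and risk, even if titer had no bearing on risk among children given the same vaccine.

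Natural exposure pulls the other way. Transmission is holoendemic (Section 4.1), and exposed adults in Mal-024 had baseline geometric mean titers of roughly 18,000 and 24,000 before any vaccine (Section 3.5.2). Natural titer can therefore mark exposure, which also raises risk. One coefficient cannot separate these components.

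This matters because the 50 µg dose was chosen on the assumption that efficacy rises with titer as a surrogate (Section 3.6.2). This model is the named analysis that bears on that assumption.

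**Working it through.** **The plan's own figure first.** The antibody model has no stated power, so the inputs come from Section 12.3: hazard 0.1155/month, 38% reduction (HR 0.62), 6 months, and 200 per arm less 20% dropout = 160 per arm.

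- Control risk: 1 − exp(−0.1155 × 6) = 0.4999.
- Vaccine risk: 1 − exp(−0.1155 × 0.62 × 6) = 0.3493.
- Events: 160 × (0.4999 + 0.3493) = 135.9.
- Schoenfeld power: Φ(√(135.9/4) × 0.478 − 1.96) = 79.6%, against roughly 80% stated. It reproduces.

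**What a titer-only model estimates when titer has no within-arm effect.** Let d be the arm difference in mean log10 titer, s the within-arm SD, and allocation 1:1. To a first approximation the log hazard ratio per log10 is

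ln(0.62) × 0.25d / (0.25d² + s²), with ln(0.62) = −0.478.

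- For d = 1.2 and s = 0.4: −0.478 × 0.30 / (0.36 + 0.16) = −0.276, HR 0.76.
- For 5-fold (d = 0.699) and s = 0.3: −0.478 × 0.1747 / (0.1221 + 0.09) = −0.394, HR 0.67.
- For 5-fold and s = 0.7: −0.478 × 0.1747 / (0.1221 + 0.49) = −0.136, HR 0.87.

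**Simulation.** There were 300 runs per setting with the same hazard, follow-up and 160 per arm. Titer was held fixed per child, which simplifies the planned time-dependent covariate. Separation and SD are assumptions. Five of the nine settings are shown, as HR per log10 (share with p<0.05):

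| Separation | Within-arm SD | Titer only | Titer + arm | Vaccinees only |
|---|---|---|---|---|
| 5-fold | 0.3 | 0.677 (57%) | 0.992 (6%) | 0.996 (6%) |
| 5-fold | 0.7 | 0.866 (26%) | 0.990 (4%) | 0.998 (4%) |
| 15-fold | 0.3 | 0.719 (72%) | 0.980 (7%) | 0.955 (6%) |
| 16-fold | 0.3 | 0.728 (69%) | 0.991 (3%) | 0.996 (6%) |
| 16-fold | 0.7 | 0.841 (46%) | 0.993 (5%) | 0.985 (5%) |

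Over all nine settings, titer only gives 0.68 to 0.87 and p<0.05 in 26% to 72%. With arm added the figures are 0.98 to 1.01 and 3% to 7%. In vaccinees only they are 0.96 to 1.01 and 3% to 6%. With 300 runs the Monte Carlo standard error at 5% is √(0.05 × 0.95/300) = 1.3 points, so the last two are compatible with the nominal level.

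**Exposure.** Assume exposure with a log-hazard SD of 0.5, a titer-exposure correlation of 0.3 to 0.5, 15-fold separation, SD 0.5, and no effect of arm or titer. The HR is 1.13 to 1.21 with titer only, 1.32 to 1.60 with arm added, and 1.33 to 1.62 in vaccinees only. An arm term does not remove exposure confounding; in this setting it exposes more of it.

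**Full mediation with the same exposure.** Let the whole vaccine effect act through titer: ln(0.62)/log10(15) = −0.478/1.176 = −0.406, a true HR of 0.67 per log10. Titer only gives 0.76 and 0.83 at correlations 0.3 and 0.5; titer plus arm gives 0.89 and 1.09.

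**The case against.** Four arguments on the other side have weight.

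**The premise is partly inferred.** Section 12.4.3 does not say that the arms are pooled or that no other covariate enters, and the RAP could add terms. A reader might infer that the plan commits to a pooled, unadjusted model; the text does not go that far. What remains is that arm terms, covariate lists and vaccinee restrictions are written out for other analyses and absent here. A RAP that elaborates the stated model would keep the problem.

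**The objective is only an association.** A crude association answers it literally, and if titer fully mediates the vaccine effect, the arm difference in titer is signal. The mediation runs bear this out: the titer-only estimate was then closer to the truth. But the titer-only model cannot show which situation holds.

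**The 16-fold figure is not an arm difference.** Section 3.5.2 reports it as a rise over the vaccinees' own baseline, about a month after dose 3. Control titers during efficacy follow-up are not given, and full-dose geometric means in Mal-014 fell from 28.4 to 14.9 thousand between Days 42 and 84. Separation is therefore shown as a range.

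**The stakes are limited.** A reader might infer that this result decides further development. Section 4.2 ties development to clinical episodes and vaccine-homologous parasitemia, the dose is already chosen, and Section 12.1.2 disclaims formal claims.

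No separate rule to use the latest earlier titer is needed, since a time-dependent covariate for subsequent risk already implies it.

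**Conclusion.** The point holds conditionally. If the model is run as written, titer would partly carry the randomized arm contrast and natural exposure. Its coefficient could then not show whether titer tracks risk beyond identifying the arm. With no within-arm effect, the apparent protection could be a hazard ratio of 0.68 to 0.87 per log10, nominally significant in about a quarter to nearly three quarters of trials. That range rests on the assumed separation and SD, the planned HR of 0.62, and titer held constant per child.

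A reader might also infer that an arm term makes the FMP1/AS02A coefficient a clean correlate of protection. The exposure runs do not support that: the within-arm coefficient remains an association. The primary test, sample size, power and alpha are untouched.

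**What to change.** State in Section 12.4.3 or the RAP, before unblinding, that the antibody-risk model is stratified by arm or includes an arm term, with titer-by-arm terms so that the slope in FMP1/AS02A recipients can be reported. Adjust for the exposure-related baseline covariates already recorded (Exhibit 7 footnotes): age, nearest field station and bed net use. Apply the same form to the fragment-specific titers. The pooled titer-only model may stay as a descriptive association. Add a sentence that residual exposure confounding remains, so the within-arm result does not prove a correlate of protection. The benefit of the adjusters was not simulated.

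No new data are needed; the cost is precision. Taking the standard error as about 1/√(events × titer variance), adding arm multiplies it by √((0.25d² + s²)/s²):

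- 5-fold, SD 0.7: √(0.612/0.49) = 1.1.
- 16-fold (d = 1.204), SD 0.3: √(0.452/0.09) = 2.2.

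The FMP1-only slope rests on 160 × 0.3493 = 55.9 of 135.9 events, a further factor of √(135.9/55.9) = 1.6.

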### Analysis of Safety

The overall percentage of subjects with at least one local AE (solicited and unsolicited) and the percentage with at least one general AE (solicited and unsolicited) during the seven-day follow-up period after vaccination will be tabulated. The incidence, intensity, and relationship of individual solicited symptoms over a seven-day period of follow‑up (day of vaccination, plus days 1, 2, 3, and 6) will be calculated for each study arm.

The number of subjects with at least one report of unsolicited AE reported up to 30 days after vaccination will be tabulated by study arm. The intensity and relationship to vaccination of the unsolicited symptoms reported will also be assessed.

SAEs are expected to be rare, but where observed will be described. Analysis of safety during the 12-month follow-up period (ten months after dose 3) will consist of comparison of incidence of SAEs as well as of changes in mean hemoglobin levels.

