## Eliciting and Documenting Adverse Events

### Definition of an Adverse Event

Reportable non-serious adverse events (RNAEs) are discussed in Section 10.1.4; serious adverse events (SAEs) are discussed in Section 10.5.

An adverse event (AE) includes any noxious, pathological, or unintended change in anatomical, physiological, or metabolic functions as indicated by physical signs, symptoms, or laboratory test abnormalities occurring in any phase of the clinical study whether associated with the study vaccine and whether considered vaccine-related. This includes an exacerbation of pre-existing conditions or events, intercurrent illnesses, a vaccine or drug interaction, or the significant worsening of a previously documented condition. A symptom present just prior to a first vaccination, and not exacerbated after the vaccination is administered, should not be considered an AE. Similarly, anticipated day-to-day fluctuations of pre-existing conditions,including the disease under study, that do not represent clinically significant exacerbations need not be considered AEs. However, discrete episodes of chronic conditions occurring during a study period (after the first vaccination) should be reported as AEs in order to assess changes in frequency or severity.

AEs should be documented in terms of a medical diagnosis. When this is not possible, an AE will be documented in terms of signs and symptoms observed by the investigator or reported by the participant at each study visit.

Pre-existing conditions, or signs and symptoms (including any that are not recognized at study entry but are recognized during the study period) that are present in a subject prior to the start of the study, should be recorded on the Medical History CRF. Any solicited sign or symptom present during a pre-vaccination assessment should be recorded on the Pre‑Vaccination Assessment CRF.

AEs that occur after informed consent is obtained, but prior to a first vaccination, will be documented on the Medical History CRF.

Any non-elective hospitalization will be considered an SAE, rather than an AE, regardless of the reason for hospitalization and possible causal relationship to vaccine administration (See Section 10.3).

Solicited AEs to be recorded are described in Section 10.1.5. Any other AEs will be recorded as unsolicited AEs.

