## Serious Adverse Events

### Definition of a Serious Adverse Event

A serious adverse event (SAE) is any untoward medical occurrence that results in death, is *life-threatening*, results in persistent or significant *disability or incapacity*, requires in-patient *hospitalization* or prolongation of existing hospitalization, or is a congenital anomaly or birth defect in the offspring of a study subject. In addition, important medical events that may require intervention to prevent one of the other outcomes listed above should be considered serious. (Examples of such interventions include intensive treatment in an emergency room, out-patient clinic or at home for allergic bronchospasm; blood dyscrasias or non-febrile seizures that do not result in hospitalization; and development of drug dependency or drug abuse.)

Additionally, the following will always be reported as SAEs: (1) any clinical management involving use of parenteral antimalarials and (2) any subjects meeting the definition of severe falciparum malaria according to the 2000 World Health Organization criteria (see Section 16.6; Appendix F).

Although not considered to be SAEs, elective hospitalizations, pregnancies and cancer diagnoses should be reported in the same expedited fashion as SAEs. No pregnancies are anticipated in this pediatric study. They are categorized as a special type of AE: the reportable, non-serious adverse event (RNAE) (See Section 10.1.4).

Definitions of terms used in the above definition of an SAE are:

*Life-threatening*: An adverse event is life-threatening if the subject was at risk of death at the time of the event; it does not refer to an event that hypothetically might have caused death if it were more severe.

*Disabling or incapacitating*: An adverse event is incapacitating or disabling if the event results in a substantial disruption of the subject's ability to carry out normal life functions. This definition is not intended to include experiences of relatively minor medical significance such as headache, nausea, vomiting, diarrhea, influenza, and accidental trauma (*e.g*., sprained ankle).

*Hospitalization*: In general, hospitalization signifies that the subject has been detained (usually involving at least an overnight stay) at the hospital or emergency ward for treatment that would not have been appropriate in the physician’s office or other out-patient setting.

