### Secondary Endpoints

Because this is a Phase IIb trial, it has many secondary endpoints. Their purpose is to gain insight into the efficacy of the vaccine and to help define a primary endpoint for a confirmatory Phase III trial. They are not intended for use to make formal claims about the vaccine.

Measurements of efficacy during the EFP:

- Times to clinical episode of *P. falciparum* malaria meeting the various secondary case definitions shown in Exhibit 8
- Time to presence of asexual stage *P. falciparum* parasites during the six-month efficacy follow-up period
- Time to parasite density  50,000 asexual stage *P. falciparum* parasites per microliter of blood during the six-month efficacy follow-up period
- Number of clinical episodes of malaria, per subject, meeting the primary case definition
- Presence of MSP-1 3D7 parasites in clinical cases of malaria meeting the primary case definition
- Presence of MSP-1 3D7 parasites at a given cross-section survey time
- Time to anemia defined as Hgb < 8.0 g/dl, whether by active or passive case detection
- Proportion of subjects with anemia (Hgb < 8.0 g/dl)

Safety during the EFP:

- Occurrences of solicited AEs during a seven‑day follow-up period (vaccination day and six subsequent days) after each vaccination (five visits: vaccination day and days 1, 2, 3, and 6)
- Occurrences of unsolicited AEs during a 30-day follow-up period after each vaccination (vaccination day and 29 subsequent days)
- Occurrences of SAEs between the first vaccination and the end of the EFP

Immunogenicity during the EFP:

- Geometric means of MSP-1 Ab titers at Visits 2, 7, 12, 17, 20, and 23 (o/a Study Days 0, 29, 57, 85, 171, and 256)

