### Tertiary Endpoints

This study has many tertiary endpoints. As with the secondary endpoints, their purpose is to gain further insight into the performance of the vaccine.

Measurement of safety (during the EFP and Addendum Efficacy Follow-up Period [AEFP]):

- Occurrences of SAEs between the first vaccination and the end of the study

Measurement of immunogenicity (during the EFP and AEFP):

- Geometric means of MSP-1 Ab titers at Study Days 0, 29, 57, 85, 171, 256, and 340

Measurement of efficacy and other biological effects by either active or passive detection (during the AEFP unless otherwise noted):

- Times to first clinical episode of *P. falciparum* malaria meeting the primary case definition (EFP and AEFP combined)
- Times to first malaria episode of *P. falciparum* malaria meeting the secondary case definitions in Exhibit 8 (EFP and AEFP combined)
- Time to presence of asexual stage *P. falciparum* parasites (EFP and AEFP combined)
- Time to parasite density  50,000 asexual stage *P. falciparum* parasites per microliter of blood (EFP and AEFP combined)

Number of clinical *P. falciparum* malaria episodes, per subject, meeting the primary case definition (EFP and AEFP combined)

- Presence of MSP-1 3D7 parasites in clinical cases of malaria meeting the primary case definition (EFP and AEFP combined)
- Presence of MSP-1 3D7 parasites at a given cross-section survey time (EFP and AEFP combined)
- Vaccine-induced GIA activity
- The parasite density at each episode of malaria infection meeting the primary and secondary definitions of clinical malaria and infection (see Exhibit 8)
- *P. falciparum* malaria allele types per malaria episode, meeting the primary and secondary definitions of clinical malaria and infection (see Exhibit 8)
- Times to first observation of anemia (Hgb < 8.0 g/dl), whether by active or passive case detection (EFP and AEFP combined)
- Hgb levels at all scheduled points of collection
- Proportion of subjects with anemia (Hgb < 8.0 g/dl) at each study collection
- Proportion of subjects with a documented decline in Hgb level of ≥ 20%
- Proportion of subjects with anemia (Hgb < 8.0 g/dl) at last study collection
- Number of cases of documented decline in Hgb level from baseline to last study sample collection
- Parasite density at all scheduled points of collection
- Non-3D7 parasite densities at all scheduled points of collection
- Genotyping for multiplicity of infections
- Antibody against fragments of MSP-142

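### The 12-month SAE comparison counts malaria SAEs with all others, so efficacy against severe or parenterally treated malaria would dilute a harm signal, and cancel a modest one

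*Protocol*

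**What the plan says.** Protocol section 12.4.4 fixes the content of the long-term safety analysis: "Analysis of safety during the 12-month follow-up period (ten months after dose 3) will consist of comparison of incidence of SAEs". Hemoglobin change is the only other component named for that period. The sentence before it reads "SAEs are expected to be rare, but where observed will be described".

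Three rules bring malaria into the SAE count:

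- Section 10.5.1 always counts "any clinical management involving use of parenteral antimalarials". Under section 7.3.3 this can include uncomplicated malaria with persistent vomiting, so the category is wider than severe disease.
- Section 10.5.1 also always counts "any subjects meeting the definition of severe falciparum malaria according to the 2000 World Health Organization criteria".
- Section 10.1.1 adds: "Any non-elective hospitalization will be considered an SAE, rather than an AE, regardless of the reason for hospitalization".

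The SAE endpoints are not split either. Section 12.1.2 has "Occurrences of SAEs between the first vaccination and the end of the EFP" and section 12.1.3 has "Occurrences of SAEs between the first vaccination and the end of the study". No section sets out an SAE comparison that leaves malaria out.

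**The concern.** Sections 3.5.2 and 4.2 describe a blood-stage vaccine intended to alter clinical disease, severe disease included. If it succeeds there, fewer vaccinated children will have a malaria SAE. That benefit enters the same count that is meant to reveal harm, with the opposite sign.

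The second component does not help. Malaria also lowers hemoglobin, and anemia is itself an efficacy endpoint in section 12.1.2. Both stated measures therefore move toward no harm when the vaccine works.

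The reverse case is also unclear. If the vaccine worsened malaria, the excess would appear in the total without being identified as malaria. A reader given only the total could not tell no harm from harm partly paid for by efficacy.

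**Working it through.** **The plan's own figures.** The protocol gives no SAE rate and no power for the SAE comparison. The one design figure used here is the 38% reduction in section 12.3, and it reproduces. The control hazard is ln 2 / 6 = 0.1155 per month. The vaccine-arm six-month risk is 1 − exp(−0.1155 × 0.62 × 6) = 0.349. With 200 × 0.8 = 160 evaluable per arm, events are 160 × (0.50 + 0.349) = 135.9, and Schoenfeld power is 79.6%, against the stated figure of roughly 80%.

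**Malaria share of SAEs, s.** Section 3 reports SAEs involving malaria as follows: Mal-015, 0 of 1; Mal-020, 3 of 5; Mal-024, 4 of 10; Mal-025, 1 of 4. The total is 8 of 20, or 40%. These studies are small and differ in age and follow-up, so the range used is 20% to 60%. Some of the eight were mixed events: malaria with pneumonia in Mal-024, and malaria with urinary infection and septicemia in Mal-020. Leaving out those two gives 6 of 20 (30%), still within the range.

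**Efficacy against malaria SAEs, VE.** Assumed equal to the design's 38%.

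**Formulas.** R is the true vaccine-to-control ratio for non-malaria SAEs.

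- Observed all-SAE ratio = s(1 − VE) + (1 − s)R
- R that is fully cancelled (observed ratio 1.00) = [1 − s(1 − VE)] / (1 − s)

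At s = 0.40:

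- No harm (R = 1): 0.40 × 0.62 + 0.60 = 0.848
- Fully cancelled: (1 − 0.248) / 0.60 = 1.253
- Doubling (R = 2): 0.248 + 0.60 × 2 = 1.448

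| Malaria share s | All-SAE ratio, no harm | R fully cancelled | All-SAE ratio when R = 2 |
| --- | --- | --- | --- |
| 20% | 0.92 | 1.10 | 1.72 |
| 40% | 0.85 | 1.25 | 1.45 |
| 60% | 0.77 | 1.57 | 1.17 |

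**Power to see a doubling of non-malaria SAEs.** Inputs are 200 per arm, two-sided 0.05, s = 0.40 and VE = 38%. The control SAE risk p is an assumption. The all-SAE comparison is p against 1.448p; the non-malaria comparison is 0.6p against 1.2p.

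| Assumed control SAE risk p | All SAEs, normal approximation | Non-malaria, normal approximation | All SAEs, exact Fisher | Non-malaria, exact Fisher |
| --- | --- | --- | --- | --- |
| 5% | 15% | 30% | 11% | 22% |
| 10% | 28% | 56% | 23% | 49% |
| 20% | 55% | 88% | 51% | 86% |

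Neither comparison has much power at low SAE rates. At assumed risks of 5% and 10%, the split comparison has about twice the power of the total.

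**The case against.** **The detail belongs to the analysis plan.** Section 12.4 defers fuller detail to a Reporting and Analysis Plan, which the DSMB approves under section 13.3.2, and a breakdown of SAEs by type is ordinary content for it. This stands to the extent that a missing table is no error. But section 12.4.4 already says what the long-term analysis will consist of, and the point concerns that stated choice.

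**Other safeguards exist.** SAEs are described, each event gets a causality judgment (section 10.3), the local medical monitor reports on each SAE (13.2) and the DSMB reviews all SAEs for trends (13.3.2). These could well expose an unusual event. They are weaker for an excess of common background illness such as pneumonia, which case-by-case judgment does not reveal and an arm comparison does. The Glossary's list of those with access to assignments up to Study Day 240 does not include the DSMB, so its trend review is not shown to be by arm.

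**Malaria SAEs must stay in the total.** This stands. Vaccine-worsened malaria would show there, and the stated objective is to assess SAEs. A vaccine-related event in a parasitemic child given parenteral treatment must not drop out of the safety comparison either.

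**Stronger readings that the documents do not support.**

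- A reader might infer that any efficacy offsets harm. Primary-definition cases are normally treated orally (section 7.3.3) and are not SAEs by that fact alone. Only efficacy that reaches severe, hospitalized or parenterally treated malaria moves the count.
- A reader might infer that a large harm could vanish. With control risks of 10% malaria and 2% non-malaria SAEs, a tripling to 6% is invisible: 1 − 0.90 × 0.98 = 0.118 against 1 − 0.938 × 0.94 = 0.118. That needs malaria to be 10/12 = 83% of control SAEs, against 40% in the protocol's own history, and section 12.4.4 expects SAEs to be rare.
- A reader might extend the point to the 30-day unsolicited AE table, because malaria was so common in Mal-031. Section 12.4.4 also assesses intensity and relationship for those events, so that analysis does not rest on a count near its ceiling.

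**Conclusion.** The point holds as a matter of dilution. By rule, severe and parenterally treated malaria are SAEs; the stated long-term comparison is of SAE incidence; and no comparison without malaria is provided. Efficacy reaching those events pulls the comparison toward no harm, and hemoglobin moves the same way.

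Cancellation is complete only for modest harm: a non-malaria ratio of about 1.25 at a 40% malaria share, between 1.10 and 1.57 over shares of 20% to 60%. Larger harm is weakened rather than hidden.

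The sizes rest on three assumptions: the malaria share, taken from 20 SAEs in small earlier studies; the SAE risk in this trial, which the protocol does not give; and the transfer of the 38% reduction to malaria SAEs. Section 12.3 states that figure for first primary-definition episodes over six months after dose 3, not for SAEs over 12 months from dose 1. The direction requires only that efficacy reaches malaria SAEs.

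This does not make the all-SAE comparison wrong. It is incomplete as the only stated arm comparison of SAEs in the long-term safety analysis.

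**What to change.** In section 12.4.4, or in the Reporting and Analysis Plan before any unblinding:

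- Keep the all-SAE comparison by arm, with its present standing.
- Add by-arm comparisons of (i) SAEs excluding those that qualify only through P. falciparum malaria, and (ii) malaria SAEs, to show either benefit or enhanced disease.
- State the rule for mixed events: an SAE with malaria plus another serious diagnosis counts in (i) as well as (ii).
- Have the classification made by staff blinded to arm.

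The data are already collected for SAE reporting. The cost is one extra classification step per SAE and one more comparison to interpret. No SAE definition, reporting rule or treatment changes.
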